#### Secondary outcome measures for worker participants on long-term sick leave

##### The number of days staying at work over a 6-month period with no exit or long-term sick leave re-occurrence (main trial secondary outcome)

Once a participant is back at work, we will collect regular data from them (through monthly texts) on any subsequent sick leave taken or leaving the organisation over a 6-month period.

The following secondary outcome measures will be collected via questionnaires at baseline, 3, 6, 9 and 12 months from participant workers.

##### Mental health and quality of life measures

The Patient Health Questionnaire (PHQ-9) [45], a nine-item questionnaire, will be used to measure depression. Anxiety will be measured by the 7-item General Anxiety Disorder Questionnaire (GAD-7) [46], and burnout will be measured using the 3-item exhaustion scale from Utrecht Burnout Scale [47]. The EURO-QOL [48] questionnaire will be used to assess quality of life. Self-report information on the NHS and social care mental health and wellbeing services and employer mental health and wellbeing services will be collected [49].

##### Return to work confidence and competence

Expectations about the length of sick leave will be asked using one question, “for how long do you believe you will be on sick leave from today?”. The 11-item Return-to-work Self-Efficacy Scale [50] will be used to assess worker’s confidence to return to work. Sixteen items from the line manager competency questionnaire [51] will be used to assess worker’s perceptions of their line manager’s competence in managing the worker’s sickness absence and return to work. An identical set of questions from this questionnaire will be used with the manager to identify their actions and behaviours from their own perspective.

##### Psychosocial work measures

Three items from the Manager Communication Questions [52] will assess participant’s confidence in communicating health matters with their managers, and two items will assess communication satisfaction. Colleague support will be measured by 1 item [53], and 5 items will assess manager support [54]. Two items will assess the worker’s intention to quit [55], and the 4-item job autonomy question will be used from the Basic Psychological Needs Satisfaction at Work Scale [56, 57]. The 9-item Readiness to Stay at Work Scale [58] will be used to assess a participant’s readiness to stay in their role at work and the 15-item Job Crafting Questionnaire [59, 60] will assess the changes workers make to their job tasks. Work Productivity will be assessed by a single question asking workers about their relative productivity in the past week. A one-item job satisfaction scale will be used to assess satisfaction [61]. A four-item scale created by the research team will be used to assess the work adjustments made for the workers when they return to work.

##### Demographic information

Workers will be asked to provide demographic information including age, gender, ethnicity, job role and tenure at baseline.

#### Secondary outcome measures for managers

The following secondary outcome measures will be collected via questionnaires at baseline, 3, 6, 9 and 12 months from participant managers.

##### Experience confidence and competence with managing mental health and RTW

At baseline only, managers will be asked about their experience as a manager (three questions), any RTW training received related to long-term sickness absence (three questions) and a six-item questionnaire on the return-to-work climate within the organisation (six questions). Managers will also be asked about their confidence in managing mental health issues and promoting a mentally healthy workplace using six items [62]. Sixteen items from the manager competency scale [51] will be used to identify the actions and behaviours undertaken by the manager when supporting the worker during their sick leave and return to work. A four-item scale created by the research team will be used to assess the work adjustments made for the workers when they return to work.

##### Autonomy and job demands

Line managers will also be asked about work autonomy that will be assessed on a four-item scale [56, 57] and job demands [54].

##### Demographic information

Managers will be asked to provide demographic information on age, gender, ethnicity, job role and tenure at baseline.

### Participant appreciation

As a token of our gratitude for taking the time to complete the organisation-wide surveys, each participant will be asked if they would like to opt-in to a randomly selected, organisation-wide prize draw to win a voucher worth £50.00. For phases 2 and 3, all participants who complete all five of the worker questionnaires or all five of the manager questionnaires will be offered the opportunity to enter a further draw to win another £50 Amazon voucher. There will be two draws for the organisation-wide survey, a draw for managers and a draw for workers (four in total per organisation).

### Study outcome and data analysis

The primary outcome of this pilot trial is to determine its feasibility for a main trial. This decision will be made using a traffic light system using predefined stop-go criteria: green light—main trial feasible; amber light—main trial feasible with adjustments; and red light—main trial should not proceed. The four criteria contributing to the traffic light system include (1) recruitment rate (green light: ≥ 50% of participants invited; amber: 25–49%; red: < 25%); (2) retention (green: ≥ 70%; amber 40–69%; red: < 40%); (3) intervention completion (green: ≥ 50%; amber: 25–49%; red < 25% ); and (4) usability of intervention materials (green: completion of all intervention components ≥ 50; amber: 25–49%; red: < 25%). An RCT to study the effectiveness of the intervention will be considered feasible when all the green criteria are met. If not, adjustments for the study protocol will be formulated for amber criteria. If red criteria are met in all four points above, a full RCT will not proceed.

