### Trial feasibility and process-related outcome measures

The primary outcome of this pilot trial is to assess the feasibility of the research procedures (including recruitment, data collection, randomisation, acceptability of the intervention, retention and the presence of any adverse events) to inform the planning of a full RCT and test a full process evaluation methodology in advance of a fully powered trial. Specifically:The willingness of organisations, their workers on long-term sick leave and the line managers of those on long-term sick leave to take part in a 30-month study, and retention through follow-up (12 months) with intervention uptake and completion as primary endpoints.The potential for selection bias in control and intervention organisations as measured using participant characteristics at baseline.Intervention delivery, dose and fidelity whilst the worker is on long-term sick leave, and implementation of intervention delivery and adherence after the worker has returned to work.Acceptability of the intervention from different demographic groups (to understand what works for whom in which circumstances)Willingness and readiness of employers and their workers to adopt the proposed intervention in a manualised format (written as an instruction manual) that is flexible enough to meet individual and organisational needs in different settings.

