The corresponding criteria for determining the success of the feasibility are outlined in the study outcome and data analysis section. The Integrative Process Evaluation Framework (IPEF) [34] will be used to evaluate the IGLOo study. The IPEF integrates the Reach, Effectiveness, Adoption, Implementation and Maintenance (RE-AIM) framework [35], and the Realist Evaluation theory [36] and has been developed to understand what works for whom in multilevel interventions such as those used in the proposed study. The RE-AIM framework evaluates five implementation outcomes: reach, effectiveness, adoption (e.g. delivery), implementation (intervention fidelity, costs and use) and maintenance (e.g. acceptability). The Realist Evaluation theory guides data generation to answer the question: “What works, for whom, in what respects, to what extent, in what contexts, and how?” Thus, allowing for the differential outcomes of the intervention for specific demographic groups such as gender and Black, Asian and Minority Ethnicity (BAME) to be identified. The IPEF is therefore a comprehensive five-phased framework guiding the collection, evaluation and reporting of process outcome data during the phases of a ‘real-world’ multi-level intervention: pre-intervention, intra-intervention, implementation and follow-up. The data collection methods outlined below capture the process outcome information using IPEF. In Realist evaluation, programme logic is formulated through CMO configurations. Figure 1 provides an overview of these hypothetical CMO configurations at each level of the IGLOo model. These CMO configurations will be empirically tested and refined based on our analyses.

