#### Intra-intervention and implementation

Guided by the IPEF, we will assess the implementation of intervention activities evaluation for each intervention phase. Intervention dose and compliance will be assessed through analytics data, including number accessing online e-learning or toolkits, number of downloads of resources, completion of modules or steps and downloads of self-guide exercises. Acceptability and usability of the intervention will be assessed using questionnaires and interviews at the end of each intervention phase. The number of coaching sessions attended by phase 2/3 worker participants will be documented, and a random selection of coaching session will be audio-recorded to assess fidelity. We will ask participants to send us screenshot/copies of completed learning activities, checklists, goal-setting and action-planning sheets and other record sheets.

Structured interviews will be conducted with all participants at the end of each intervention phase with a view to explore the mechanisms by which the intervention works. For example, we will explore how participants have attempted to transfer knowledge, skills and methods learned from each intervention phase within their respective roles (e.g. as a leader implementing policies, as a line manager supporting a worker on sick leave, and as a worker requesting work adjustments). Questionnaires and interviews will also be used to understand intentions and motivations for intervention engagement, changes to cognitions and behaviours as a result of the intervention, and any contextual factors (barriers and facilitators) that may have influenced engagement with the intervention materials.

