### Process evaluation analysis plan

Process evaluation analyses will be guided by IPEF. Quantitative process data will primarily take the form of simple descriptive statistics (e.g. proportions and percentages, means and standard deviations). Qualitative interview data will be transcribed verbatim and analysed using inductive thematic analysis procedures. Quantitative and qualitative data will be triangulated and systematically coded using the core theoretical frameworks to identify the change mechanisms of how leaders, workers and line managers translate the intervention materials into behaviour changes and the barriers and facilitators in doing so. This will provide us with valuable information on what works and under what context (e.g. readiness for change, culture) and how these lead to our intended outcomes.

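### Stop-go criterion 4 is named usability but scored by completion of all components, so no usability result sets any of the four lights

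*Protocol article*

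**What the plan says.** All references are to the Protocol article.

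*Study outcome and data analysis* states that the pilot's primary outcome is feasibility for a main trial, decided by predefined stop-go criteria, and lists four: recruitment rate, retention, intervention completion, and a fourth worded "usability of intervention materials (green: completion of all intervention components". Criteria 3 and 4 share their cut-offs: green from 50%, amber 25–49%, red below 25%. The main trial counts as feasible when every criterion is green. Otherwise "adjustments for the study protocol will be formulated for amber criteria". A full trial is ruled out if all four are red.

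*Trial feasibility and process-related outcome measures* sends the reader to that list: "The corresponding criteria for determining the success of the feasibility are outlined in the study outcome and data analysis section". It also counts acceptability of the intervention within the primary feasibility outcome, and describes willingness to take part and retention "with intervention uptake and completion as primary endpoints".

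*Intra-intervention and implementation* says how each construct is measured. On exposure: "Intervention dose and compliance will be assessed through analytics data, including number accessing online e-learning or toolkits", continuing to "completion of modules or steps and downloads of self-guide exercises". On usability, in the next sentence: "Acceptability and usability of the intervention will be assessed using questionnaires and interviews at the end of each intervention phase".

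*Process evaluation analysis plan* adds that "Quantitative and qualitative data will be triangulated and systematically coded using the core theoretical frameworks".

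**The concern.** The protocol separates two constructs and their data sources, then scores one under the other's name. Finishing the components is a measure of exposure. Whether people found the materials workable is a judgement that the protocol plans to collect from them directly. A participant can finish materials that were hard to use, or find them easy and stop for reasons unrelated to them, which is plausible in people on long-term sick leave.

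This matters because the lights are the pilot's primary result. A green light 4 would be reported as evidence that the materials are usable, although no usability result had been tested against a threshold. A light below green would be reported as a usability shortfall when the measured shortfall is in full completion.

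**Working it through.** No sample size, power or effect figure is at issue, so the check is a comparison of wording followed by the logic of the decision rule.

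**1. Name, input and source of each light**

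| Light | Name | What sets it | A usability rating enters? |
|---|---|---|---|
| 1 | Recruitment rate | Share of those invited who are recruited | No |
| 2 | Retention | Share retained | No |
| 3 | Intervention completion | Share completing | No |
| 4 | Usability of materials | Share completing all components | No |

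Lights set by completion: 2 of 4. Lights set by a usability result: 0 of 4.

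**2. Is completion the protocol's own measure of usability?** No. *Intra-intervention and implementation* lists completion of modules or steps among the analytics for dose and compliance, and gives usability its own instruments. Intervention components also include coaching, whose attendance that section records separately from the analytics. Attendance is again a count of exposure, so including it does not make light 4 a usability measure.

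**3. What the rule does with a usability result.** Let c be the number completing all components, n the denominator and u the number rating the materials usable. Light 4 depends on c/n only. For illustration take n = 50, the target number of intervention workers in *Sample size*. The denominator is an assumption, and it leaves out managers and leaders, who also receive materials.

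- c = 25: 25/50 = 50%, green.
- c = 12: 12/50 = 24%, red.
- In both cases u may be anything from 0 to 50 and the colour is the same.

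Lights 1 to 3 do not contain u either, so the overall result does not depend on it.

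**4. How far lights 3 and 4 overlap.** This depends on definitions that the article does not give. Of the 3 × 3 = 9 colour pairs:

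- the same count for both lights: 3 can occur (both red, both amber, both green);
- full completers a subset of light 3's completers, on the same denominator: 6 can occur, since light 4 cannot then be better than light 3;
- different groups: all 9 can occur.

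The finding in step 1 holds in all three cases.

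**5. Reach within the decision.** All-green needs light 4 green, so full completion below 50% withholds that result whatever users report. A stop needs all four red, so a red light 4 counts towards a stop only when the other three are red as well.

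**The case against.** The best defence has four parts.

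- **The metric is disclosed.** The scoring rule stands in the same parenthesis as the label, and full completion of self-led online materials is a conceivable behavioural proxy for usability. The disclosure is real and limits the harm to a careful reader. But the protocol nowhere calls completion a proxy, gives usability its own instruments, and already has a completion light. Making completion a primary endpoint justifies one such light, which criterion 3 supplies.
- **Usability evidence is not lost.** This stands. End-of-phase questionnaires and interviews are triangulated with the quantitative data in the process evaluation. A reader might infer that an amber light 4 would leave the team unable to tell whether the materials or the uptake need changing. The documents do not support that: the amber rule does not confine adjustments to evidence from the light, and the interviews cover barriers to and facilitators of engagement.
- **The decision is not hostage to light 4.** This also stands. A red light 4 by itself cannot rule out the main trial.
- **The article is condensed.** A reader might fault criteria 3 and 4 for lacking full definitions and denominators. An article commonly leaves those to the full protocol or analysis plan, so they are no finding here. For the same reason it cannot be claimed that lights 3 and 4 always agree. The mismatch between name and metric is different: both are stated, and they conflict.

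**Conclusion.** The point holds as a mislabelled decision criterion. As written, two of the four lights measure completion, none uses a usability result, and a green light 4 would claim something that was not tested against a threshold. This rests on the article's wording alone, apart from reading the 50 in criterion 4 as 50%. The 25-of-50 and 12-of-50 figures are illustrations on an assumed denominator.

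The consequence is limited to whether the pilot is reported as all-green or needing adjustment, and to what that report is said to show about usability. It does not invalidate the pilot, and the usability data will still be collected and used. It should be corrected because the lights are the primary outcome and the correction is cheap.

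**What to change.** 1. Relabel criterion 4 as completion of all components, or merge it with criterion 3.
2. Base the usability criterion on the end-of-phase usability questionnaire already planned. Fix the item and the green, amber and red cut-offs before any responses are seen.
3. Score it among respondents who accessed the materials, and print the response rate beside the light. Non-respondents should not be counted as finding the materials unusable, because that would mix usability with engagement again.
4. Keep the closing rule in step with the list. Merging criteria 3 and 4 and adding usability leaves four. Relabelling criterion 4 and adding usability makes five, and the rule that refers to all four points must then be reworded.

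The cost is a change to one or two criteria and their cut-offs, plus a check of the questionnaires. Table 2 lists intervention acceptability only among the phase 1 leader measures and shows no usability item for workers or managers, so one must be confirmed or added there. The drawback is that self-ratings are open to non-response, whereas module completion can be counted from analytics. That is why the response rate has to accompany the light.

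### The traffic-light rule gives no consequence for one, two or three red criteria, so the pilot's primary go/no-go decision is only partly predefined

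*Protocol article*

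**What the plan says.** All of the relevant text is in the protocol article, section Study outcome and data analysis. The section Trial feasibility and process-related outcome measures names feasibility as the primary outcome and refers the reader there for the success criteria.

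The section calls its stop-go criteria predefined. It describes three lights: green (main trial feasible), amber (feasible with adjustments) and red, given as "red light—main trial should not proceed". It then sets bands for four criteria:

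| Criterion | Green | Amber | Red |
|---|---|---|---|
| 1. Recruitment, of those invited | ≥ 50% | 25–49% | < 25% |
| 2. Retention | ≥ 70% | 40–69% | < 40% |
| 3. Intervention completion | ≥ 50% | 25–49% | < 25% |
| 4. Usability, measured as completion of all components | ≥ 50 | 25–49% | < 25% |

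Three sentences turn these into a decision. The full RCT counts as feasible when every criterion is green. Next comes "If not, adjustments for the study protocol will be formulated for amber criteria". Last comes "If red criteria are met in all four points above, a full RCT will not proceed".

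**The concern.** Each criterion has its own red cut-off, and red is said to mean that the main trial should not go ahead. Yet a red on one, two or three criteria leads nowhere: the all-green test fails, the stop sentence does not apply, and the adjustment sentence covers amber criteria only.

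The point of fixing progression criteria in advance is that the decision does not depend on how the results look. Where the rule is silent, the team has to decide, after seeing the data, whether a failed criterion is fatal, repairable or ignorable. Here that decision is the pilot's primary outcome.

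A single red is not far-fetched. The Sample size section aims for 30 workers from each of eight organisations, so that 50 per arm remain even with high attrition. That tolerates 100/(8 × 30) = 100/240 = 41.7% retained, less than two percentage points above the red line for retention. This is a tolerance and not a forecast, but it shows that the plan allows for results close to a red boundary.

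**Working it through.** The document gives no figure to reproduce. The check is to list every possible result and apply the three decision sentences as written.

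**Inputs.** Four criteria and three colours each, from Study outcome and data analysis.

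**Patterns.** 3^4 = 81.

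- All green: 1. Feasible.
- No red, at least one amber: 2^4 − 1 = 15. Adjust.
- All red: 1. Stop.
- One to three reds: 81 − 1 − 15 − 1 = 64. No consequence stated for the red criteria.

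**The 64 by number of reds.** Choose which criteria are red, then let each of the others be green or amber.

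- One red: 4 × 2^3 = 32
- Two reds: 6 × 2^2 = 24
- Three reds: 4 × 2^1 = 8
- Sum: 32 + 24 + 8 = 64

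**The 64 by whether any sentence applies.** Patterns with reds and greens only, excluding all green and all red: 2^4 − 2 = 14. Here no criterion is amber, so the adjustment sentence has nothing to act on and no outcome follows. The other 64 − 14 = 50 contain an amber, so the adjustment sentence applies to that criterion but is silent on the red one.

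**Overlap of criteria 3 and 4.** Both are measured by completion. If they always took the same colour, there would be 3^3 = 27 patterns: 1 all green, 2^3 − 1 = 7 adjust, 1 all red and 27 − 9 = 18 with some but not all red. Of those 18, 2^3 − 2 = 6 have no amber. The gap does not depend on treating the two as separate.

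**One case followed through.** Recruitment below 25%, retention below 40%, both completion criteria at 50% or more:

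- Feasible? No, two criteria are not green.
- Adjust? No criterion is amber.
- Stop? No, only two of four are red.

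**Same count under a worst-light rule.** If any red gave an overall red: 1 proceed, 15 adjust, 65 red (64 + 1), none undefined.

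**The case against.** Several points on the other side are sound.

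*Red light may mean only the overall verdict.* The three lights are introduced as verdicts on the main trial, and the criteria are said to feed into them: "The four criteria contributing to the traffic light system include". On that reading the stop sentence just says how an overall red arises, and nothing is contradicted. Against this, the first criterion uses the word light for itself: "recruitment rate (green light: ≥ 50% of participants invited; amber: 25–49%; red: < 25" (per cent). The wording supports either reading. A reader might infer a flat self-contradiction, but that follows only if red light applies to single criteria. The missing rule for one to three reds holds on both readings.

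*A failed trial is not waved through.* A reader might infer that a pilot with up to three reds goes forward. The text does not say so: any red fails the all-green test, so such a pilot is never declared feasible. What can be said is that it is not stopped either.

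*Most mixed patterns trigger something.* In 50 of the 64 the adjustment sentence is engaged through an amber criterion. One could also read its opening words as sending every mixed result to the middle category, in which case only the restriction to amber criteria is too narrow. This is fair, but on the wording as it stands the red criteria still have no stated consequence.

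*Lenience can be deliberate.* Requiring every criterion to fail before automatic abandonment, with judgement in between, is a possible choice for a pilot. But the plan does not state that judgement applies in between, or on what basis.

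*An unseen document may cover it.* The article does not leave the rule to another document; it states the rule, including the stop condition, and the stated rule is incomplete.

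**Conclusion.** The point stands as an incomplete combining rule for the primary outcome: 64 of 81 colour patterns leave the red criteria without a consequence, and 14 of those match no decision sentence. This rests only on the published wording and on each criterion being able to take any of its three colours. If criteria 3 and 4 always agree, the counts are 18 of 27 and 6 of 27.

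Two stronger inferences are not supported. First, 64/81 = 79% is not the chance of an undefined result; the patterns are not equally likely, and those that separate criteria 3 and 4 widely are implausible. Second, one cannot say that the stop rule is practically unreachable. With an assumed chance p of red on each criterion, independence gives p^4, from 0.0001 at p = 0.1 to 0.0625 at p = 0.5. If all four criteria moved together, it would be p itself, 0.1 to 0.5. The documents give neither p nor the dependence.

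This should be fixed, but it does not threaten the pilot's conduct. Randomisation, data collection and the outcome analyses are unaffected, and all four rates can still be reported against their cut-offs. What is lost is the claim that the decision was predefined.

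**What to change.** Before data are seen, replace the last decision sentence with a rule that assigns an outcome to every combination and agrees with the stated meaning of red. One form is that the overall light is the worst single light:

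- Any red: the main trial does not proceed in its present form, unless a specific remedy for that criterion is documented.
- No red, at least one amber: proceed with adjustments.
- All green: proceed.

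A more lenient rule would also close the gap, provided that it states the outcome for one, two and three reds and that the definition of a red light is reworded to match. The rule should name who accepts a remedy; the governance section lists the Trial Steering Committee's members but gives it no role in this decision.

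A minor wording point can be settled at the same time. The bands have gaps between whole percentages, so amber could read 25% to below 50%, and 40% to below 70% for retention.

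The cost is a few sentences. The downside of the worst-light form is that it is stricter, so an unqualified decision to proceed becomes less likely.
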